#### Settings and Participants

Schools were contacted from a database containing all schools located in the broad geographical area of East London. Of the schools approached, a total of 10 primary schools in East London across 5 boroughs were recruited. These boroughs (Waltham Forest, Havering, Redbridge, Newham, and Tower Hamlets) include among the most densely populated, socioeconomically, and ethnically diverse areas in London [11].

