#### Sample Size

Based on the planned analyses, the target recruitment was 1200 children in school years 3-5 (age 7-11 years). This sample size provides (1) 94% power to detect correlations as small as 0.10 (2-tailed), *P*<.05 between resilience measures and correlates and (2) the opportunity to compare groups high and low on a psychological or social factors (eg, top and bottom 20% of the sample on attention control) or on a resilience measure and to detect even small effects (eg, Cohen *d*=0.30) at 90% power, 2-tailed, *P*<.05.

Importantly, this sample size will enable us to use novel data-driven analytic approaches to identify subpopulations with different resilience trajectories across time and to assess the predictive value of different psychosocial variables (main effects, interactions, mediation effects) on resilient trajectories by using multinomial logistic regression. This will also allow us to use other advanced quantitative analyses, including structural equation modelling (to explore mediation and moderation effects), a combination of exploratory and confirmatory factor analysis (to verify the factor structure of selected questionnaires), and network analysis to explore associations between individual items of questionnaires.

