### Procedures

Schools provided the team with students who met the inclusion and exclusion criteria and the students who the teachers felt would struggle to complete measures in a group setting. During data collection visits, researchers provide further information about the DEER study to pupils, and pupils provide written assent before completing a battery of validated questionnaires. All assessments intended for the child to complete are done in the classroom, mainly on an electronic tablet or pen and paper depending on the task, in small groups but with privacy. As the baseline assessment took up to 4.5 hours to complete, site visits were often split up across multiple sessions. Detailed information was collected about the demographics as well as the social, personal, and community factors affecting resilience in children. Trained researchers were present throughout all sessions to explain procedures and answer questions. All baseline questionnaires were administered between October 2022 and December 2023. Follow-up will be conducted at least annually until the first term of the secondary school (where possible). Parents or carers complete a set of web-based questionnaires for each year their child is enrolled in the study, for which they received financial reimbursement in the form of e-vouchers worth £10 (US $13.74). Teachers are also asked to complete paper questionnaires for each pupil enrolled in the study and to describe the provision of mental health services at the school.

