#### Teachers’ Measures

Table 4 [45,50] shows the list of measures that teachers will complete about their children.

**Table 4 table4:** List of measures that teachers will complete about children.

Name of the scale	Brief description	Style of administration
The Strengths and Difficulties Questionnaire [45]	The questionnaire asks about the teacher’s report on students’ emotional symptoms, conduct problems, hyperactivity/inattention, peer relationship problems, and prosocial behavior.	Pen and paper
Amended: Questionnaire about school resources for mental health support [50]	The questionnaire will ask about all the different resources available to students that are provided by the school for mental health support. Questions about creative arts therapies have been added.	Online platform

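### The stated 94% and 90% power assume independent children, although children are clustered in 10 schools; the figures cannot hold for school-level correlates

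*Protocol article*

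**What the plan says.** Sample Size sets the target: "the target recruitment was 1200 children in school years 3-5 (age 7-11 years". It claims "94% power to detect correlations as small as 0.10 (2-tailed") between resilience measures and their correlates, without restricting the level of the correlate. It also claims enough children to compare the highest and lowest fifths on a factor and "to detect even small effects (eg, Cohen *d*=0.30) at 90% power". The same section says the sample will allow the team "to assess the predictive value of different psychosocial variables (main effects, interactions, mediation effects) on resilient trajectories by using multinomial logistic regression", and adds structural equation, factor and network models. It mentions no ICC, design effect, school or class.

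Other sections describe a clustered sample:

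- Settings and Participants: "a total of 10 primary schools in East London across 5 boroughs were recruited".
- Procedures: "Teachers are also asked to complete paper questionnaires for each pupil enrolled in the study".
- Teachers' Measures, on the school provision questionnaire: "The questionnaire will ask about all the different resources available to students that are provided by the school for mental health support".
- Consenting Process: six schools were opt-in only, three opt-out only, and one moved from opt-in to opt-out.
- Planned Analyses: the opt-in versus opt-out comparison is a key analysis. A significant result decides whether later papers add a sensitivity analysis. Specific analyses are left to individual preregistrations.
- Results: 873 children were enrolled.

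**The concern.** Children in one school share intake, neighbourhood and staff, and children in one class may share a rater. Their responses are therefore likely to be correlated, and a power figure for independent children overstates the information in the sample. How far depends on the predictor. For a characteristic that varies mostly within schools, the loss may be small. For one fixed by school there are only 10 independent values, however many children are enrolled.

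The second case matters here because the study sets out to learn which resources contribute to resilience, and school mental health provision is measured as one of them. Consent route is also set by school in nine of the ten schools, and the significance of that comparison steers later papers. If a test ignored school it would reject too often; if it respected school it would often miss a real difference.

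**Working it through.** **Inputs from the article.** N=1200 (target) and 873 (enrolled); 10 schools, so a mean m of 120 or 87.3 children per school; r=0.10; d=0.30; two-sided alpha 0.05.

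**Assumed.** The article gives no ICC. School ICCs of 0.01 to 0.10 and equal school sizes are assumed; unequal sizes would make matters somewhat worse.

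**1. The stated figures, children independent.**

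- Correlation, Fisher z: power = Φ(atanh(0.10)·√(N−3) − 1.96). At 1200: Φ(3.471 − 1.96) = 93.5% (stated: 94%).
- Extreme groups: 20% of 1200 = 240 per group; Φ(0.30·√(240/2) − 1.96) = Φ(3.286 − 1.96) = 90.8%, or 90.7% by noncentral t (stated: 90%).

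Both reproduce with no clustering allowance. At 873, still independent: Φ(2.959 − 1.96) = 84% for r=0.10, and 80% for d=0.30 with about 175 per group.

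**2. Child-level predictor.** Design effect DE = 1 + (m−1)·ICCx·ICCy; effective N = N/DE; power by Fisher z as above. If clustering were ignored, type I error ≈ 2·[1 − Φ(1.96/√DE)].

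| Both ICCs | N | DE | Effective N | Power, r=0.10 | Type I if ignored |
|---|---|---|---|---|---|
| 0.02 | 1200 | 1.05 | 1145 | 92% | 5.5% |
| 0.05 | 1200 | 1.30 | 925 | 86% | 8.5% |
| 0.10 | 1200 | 2.19 | 548 | 65% | 18.5% |
| 0.02 | 873 | 1.03 | 844 | 83% | 5.4% |
| 0.05 | 873 | 1.22 | 718 | 77% | 7.5% |
| 0.10 | 873 | 1.86 | 469 | 58% | 15% |

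**3. School-level predictor.** ICCx = 1, so DE = 1 + (m−1)·ICCy. Power from a noncentral t on 10 − 2 = 8 df, critical value 2.306, noncentrality [r/√(1−r²)]·√(effective N).

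| Outcome ICC | N | DE | Effective N | Power, r=0.10 | Type I if ignored |
|---|---|---|---|---|---|
| 0.01 | 1200 | 2.19 | 548 | 54% | 18.5% |
| 0.02 | 1200 | 3.38 | 355 | 39% | 29% |
| 0.05 | 1200 | 6.95 | 173 | 21% | 46% |
| 0.01 | 873 | 1.86 | 469 | 48% | 15% |
| 0.02 | 873 | 2.73 | 320 | 35% | 24% |
| 0.05 | 873 | 5.32 | 164 | 21% | 40% |

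More children would not rescue this. With 10 schools, effective N cannot exceed 10/ICC: 1000 at ICC 0.01 and 200 at ICC 0.05. The stated 94% needs about 1200 independent units.

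**4. Consent route, illustration.** Count the mixed school as opt-out, giving 6 v 4 schools. SE = √{[ICC + (1−ICC)/m]·(1/6 + 1/4)}. At N=873 and ICC 0.05: SE = √(0.0609 × 0.4167) = 0.159, noncentrality 0.30/0.159 = 1.88, power 38% on 8 df. At ICC 0.02 and 0.10 it is 64% and 24%.

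**5. Teacher ratings.** With 10 to 25 rated children per class and class ICC 0.05 to 0.20 (both assumed), DE for a class-constant predictor runs from 1 + 9×0.05 = 1.45 to 1 + 24×0.20 = 5.80.

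**The case against.** A reader might infer that the named analyses treat children as independent, so that the standard errors will be too small. The article does not support that. It lists families of model, each of which can carry cluster terms or cluster-adjusted errors, and leaves specification to preregistration. Silence on cluster terms is ordinary in a condensed article. The type I error figures above therefore apply only if clustering is left out.

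It can also be said that the power statement was never meant for school-level factors: its example is attention control, most measures concern individual children, and the loss at low ICCs is small. That is fair for child-level associations. With both ICCs at 0.02, power at 1200 is 92%, close to the stated value. The enrolment shortfall should also be kept apart from clustering: at 873 independence already gives 84%, so with both ICCs at 0.05 clustering costs about 7 points (84% to 77%), not 17. But the claim about correlates carries no limit, and school provision and consent route are among the variables to be studied.

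Finally, requiring school fixed effects in every paper would be a debatable remedy. It would remove the between-school variation that the study may want to examine, and it would cost nine parameters per non-reference class in a multinomial model. That objection stands, and no such default is proposed.

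**Conclusion.** The power statement is wrong as a description of this design: it is an independent-sample calculation for a sample drawn through 10 schools. For child-level associations the error is slight at ICCs near 0.02 and material from about 0.05 upward. For school-level correlates the quoted power is out of reach at any assumed outcome ICC of 0.01 or more, with about 54% to 21% at the target and 48% to 21% at the enrolled number for ICC 0.01 to 0.05. If clustering were ignored at 873, type I error would be about 5% to 15% for child-level predictors (both ICCs 0.02 to 0.10) and 15% to 40% for school-level ones (outcome ICC 0.01 to 0.05). All of this rests on assumed ICCs and equal school sizes. That the analyses will in fact ignore clustering is not established. Preregistration can settle the model, but it cannot correct the published power figures or add schools.

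**What to change.** In Sample Size:

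- State that both power figures assume independent children and apply only to child-level associations.
- Restate them at the enrolled 873 over a declared ICC range.
- Label school-level analyses, including opt-in versus opt-out, as exploratory and resting on 10 units.

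In Planned Analyses, require each preregistration to commit to an analysis that accounts for school, and for class or teacher where teachers are the raters. The method should be valid with about 10 clusters, for which ordinary sandwich errors are unreliable, and suited to the model used. For example, Kenward-Roger belongs to linear mixed models and not to multinomial logistic regression. The choice between fixed and random school effects can stay with each paper, according to whether between-school variation is part of its question.

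The cost is wording, a less favourable stated power and somewhat wider intervals. No new data are needed, and with follow-up planned to June 2027 later papers can still adopt it.

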### Ethical Considerations

This study has been reviewed and approved by the Queen Mary University of London research ethics committee (QMERC22.251) on June 27, 2022. The study was prospectively registered in the International Standard Randomized Controlled Trial Number registry (ISRCTN14396374). Written assent from the children was obtained prior to any study procedures being conducted, and written consent was obtained from parents/carers if children were recruited via opt-in procedures. All participating schools gave written consent for participation via the school principals. To ensure anonymity, study data are stored in a deidentified format. Names and other identifying information (eg, addresses, contact details) are replaced by a unique participant ID number. To reduce the risk of disclosure, participant identifying information is stored separately from the research data, which will be saved on a secure server at the Youth Resilience Unit, hosted by Queen Mary University of London. To say thank you to the child’s class for taking part, we offer participation in an interactive science show organized by the Centre of the Cell, Queen Mary University of London. The show is aimed at children in primary schools and is educational and fun. Whether the show is offered at the school or the school attends the Centre of the Cell is decided by the school. We compensate parents who complete annual questionnaires £10 (US $13.74) each time.

### Procedures

Schools provided the team with students who met the inclusion and exclusion criteria and the students who the teachers felt would struggle to complete measures in a group setting. During data collection visits, researchers provide further information about the DEER study to pupils, and pupils provide written assent before completing a battery of validated questionnaires. All assessments intended for the child to complete are done in the classroom, mainly on an electronic tablet or pen and paper depending on the task, in small groups but with privacy. As the baseline assessment took up to 4.5 hours to complete, site visits were often split up across multiple sessions. Detailed information was collected about the demographics as well as the social, personal, and community factors affecting resilience in children. Trained researchers were present throughout all sessions to explain procedures and answer questions. All baseline questionnaires were administered between October 2022 and December 2023. Follow-up will be conducted at least annually until the first term of the secondary school (where possible). Parents or carers complete a set of web-based questionnaires for each year their child is enrolled in the study, for which they received financial reimbursement in the form of e-vouchers worth £10 (US $13.74). Teachers are also asked to complete paper questionnaires for each pupil enrolled in the study and to describe the provision of mental health services at the school.

### Measures

#### Design of Measures

Most outcome measures are completed via tablet computers by using data management applications (eg, Qualtrics, Research Electronic Data Capture [REDCap]). Qualitative measures are completed on paper. A paper-based case report form is used to keep track of the completion of measures for each participant. This study takes place in schools with children, and so the assessment schedule may need to be adapted to fit the practical demands of the environment. As this is a longitudinal cohort, some measures may be dropped, and new measures may be introduced in response to new knowledge, new substudies, or changes to the factors of interest. This may include changing measures that children report to be too time-consuming or onerous to complete within the allocated time. All changes to the measures will be reviewed and approved by the ethics committee prior to implementation.

#### Measures About Resilience and Mental Health

Table 1 [12-24] shows the measures we used to analyze resilience and the mental health of the children.

**Table 1 table1:** Measures about resilience and mental health.

Name of the scale	Brief description	Style of administration
Demographics	We will be asking children to report their gender, age, and height and weight will be measured	Tablet
The Stirling Children’s Well-Being Scale [12]	Self-report questionnaire used to assess children’s emotional and psychological well-being	Tablet
The University of California Los Angeles 3-Item Loneliness Scale adapted to 10-15-year old children and Office for National Statistics, United Kingdom, 1-item Direct Measure of Loneliness [13,14]	Self-report questionnaire used to measure feelings of loneliness and social isolation	Tablet
The Revised Child Anxiety and Depression Scale [15]	Self-report questionnaire providing an overall internalizing score and subscores assessing anxiety (social phobia, panic disorder, separation anxiety, generalized anxiety, obsessive-compulsive symptoms) and symptoms of depression	Tablet
The Children’s Revised Impact of Event Scale [16,17]	A self-report questionnaire designed to screen for posttraumatic stress symptoms in children	Tablet
Body Mapping protocol [18]	Body mapping, an arts-based research method, adapted for use to understand how children make sense of their own stress and resilience	Pen and paper
Connor-Davidson Resilience Scale [19]	Self-report questionnaire assessing resilience	Tablet
The Revised Child and Youth Resilience Measure [20]	Self-report questionnaire assessing resilience	Tablet
The Student Life Satisfaction Scale [21,22]	Self-report questionnaire used to gauge an overall level of life satisfaction among children	Tablet
The Somatic Complaints List [23]	Self-report psychosomatic questionnaire used to identify how often children experience and feel pain	Tablet
The Self-Perception Profile for children [24]	Self-report questionnaire used to measure a school-age child’s sense of general self-worth and self-competence in the domain of academic skills (scholastic competence, social competence, athletic competence, physical appearance, behavioral conduct, and global self-worth)	Tablet

#### Measures About Resources, Psychological, and Social Factors

Table 2 [25-42] shows all the measures used for measuring the psychological factors, social factors, and the resources available to children.

**Table 2 table2:** List of measures used for measuring the psychological factors, social factors, and resources available to children.

Name of the scale	Brief description	Style of administration
Short version of The Cognitive Emotion Regulation Questionnaire [25,26]	Self-report questionnaire assessing emotional regulation and cognitive copying strategies (self-blame, other blame, acceptance, planning, positive refocusing, rumination or focus on thought, positive reappraisal, putting into perspective, and catastrophizing).	Tablet
Social connectedness questionnaire [27]	A questionnaire exploring children’s global social connectedness, within the domains of family, school, peer, and community connectedness.	Tablet
The Advanced Theory of Mind battery [28]	Selected tasks from a task battery used to measure children’s ability on social reasoning and recognizing transgression.	Tablet
The Children’s Leisure Activities Study Survey [29]	Self-report questionnaire used to gain an understanding about participants’ engagement with leisurely activities, hobbies, and exercise.	Tablet
The Youth Spirituality Scale [30]	Self-report questionnaire assessing children’s connections to God or higher power as well as their relationship with religious practices. For this purpose, we will look at the Relationship with God and Religious Practices subscales only.	Tablet
The Ambiguous Story Paradigm [31]	A task used to assess children’s tendencies to select negative over benign interpretations of ambiguous situations.	Tablet
The Adapted Prospective Imagery Task [32]	A task used to assess children’s capacity to imagine past and future positive and negative events in detail.	Tablet
Self-Esteem Matrix Task [33,34]	The task is used to measure how quickly participants can find an accepting face (smiling face) in a matrix of 15 rejecting faces. Slower reaction times on this task may suggest higher sensitivity to social threats.	Tablet
The Five Field Map [35]	Self-report questionnaire used to gauge the size of the children’s social network as well as to uncover more details surrounding their relationships.	Pen and paper
The Pictorial Personality Traits Questionnaire for Children [36]	Self-report questionnaire that uses images to explore children’s personality traits, underpinned by the Big 5 Personality Traits theory.	Tablet
The approach-avoidance task [37]	A task used to index children’s approach and avoidance of emotional faces (angry vs happy).	Tablet
The Youth Life Orientation Test [38]	Self-report questionnaire assessing optimism and pessimism.	Tablet
The Scrambled Sentences Task [39,40]	A task used to assess interpretations of ambiguous sentences.	Tablet
Door Opening Task [41,42]	A computerized response perseveration task aimed at studying reward dominance in children.	Tablet
Words for Feeling Questionnaire	Used to measure children’s emotional vocabulary. Children are asked to come up with different synonyms of emotional words (eg, surprised, happy, scared).	Pen and paper

#### Parents’/Carers’ Measures

Table 3 shows the list of measures that parents/carers will complete about their children [43-49].

**Table 3 table3:** List of measures that parents/carers will complete about children.

Name of the scale	Brief description	Style of administration
Demographics and socioeconomic status questionnaire	Questions will ask about the child’s date of birth, sex, ethnicity, country of birth, and number of siblings. We will also include questions about socioeconomic status, child’s religion, family migration status, family structure (ie, foster family, single parent, nuclear family), carers’ relationship to the child (ie, biological, foster or adoptive mother or father), household number, the child’s birth order, diet type they primarily follow, if the child has ever been in the care of local authority (ie, in foster or residential care), and if the child or anyone in their immediate family has ever been formally diagnosed with a mental health disorder. Socioeconomic status questions will include items relating to the carers’ education, occupation, material possessions, whether the child receives free school meals, type of accommodation, and post code (to ascertain material deprivation index).	Online platform
Patient Health Questionnaire 15 [43]	These measures link to physical health problems, including any chronic illness or disability, pain, fatigue, and sleep. For the Patient Health Questionnaire, we will only use questions relevant to physical health problems.	Online platform
Child Health Utility instrument 9D [44]	The Child Health Utility instrument is a pediatric generic preference-based measure of health-related quality of life—we will be using a proxy version for parents to complete. We will also be using questions formulated in-house to ascertain key factors such as hospitalization rates and birth weight.	Online platform
The Strengths and Difficulties Questionnaire [45]	The questionnaire asks about the parents or carers report on their child emotional symptoms, conduct problems, hyperactivity/inattention, peer relationship problems, and prosocial behavior.	Online platform
Arts Council Questionnaire The Taking Part Survey [46]	The survey collects information about children and adults’ attendance at a wide variety of arts events, museums, galleries, libraries, and heritage sites. It also asks about participation in creative activities and sport and motivations and barriers to engagement.	Online platform
The Children’s Life Events Inventory [47]	Questionnaire used to identify the number of significant life events experienced by the child.	Online platform
The Parenting Styles and Dimensions Questionnaire [48]	Questionnaire used to assess parenting styles that we will be using in the short version of this scale. It measures 3 types of parenting styles: authoritative, authoritarian, and permissive parenting.	Online platform
Parental report of their children social media usage	Questionnaire asking about children’s social media use.	Online platform
The Child version of the Eating Disorder Examination [49]	The Child version of the Eating Disorder Examination questionnaire provides assessment of eating disorder psychopathology related to anorexia nervosa, bulimia nervosa, and binge-eating disorder; however, the Child version of the Eating Disorder Examination questionnaire-8 items does not assess symptoms of avoidant/restrictive food intake disorder, pica, or rumination disorder. Originally, this is a self-report questionnaire, but we will use it as a parent/carer report format.	Online platform

